#### Additional measures

City-level data on air quality, weather, climate, green spaces, and pollution are collected through available open data.

#### Evaluation of implementation

To evaluate the implementation of the WELLBASED programme, the Reach, Effectiveness, Adoption, Implementation, and Maintenance (RE-AIM) framework is adopted [39]. Indicators such as reach (number and proportion of individuals willing to participate), adoption (number of intervention agents willing to initiate the intervention), implementation (percent of program delivery, adaptation and costs) and maintenance (long-term adaptation of the intervention) are assessed. Both qualitative and quantitative methods are applied to collect information on implementation of the WELLBASED program across study sites.

### Power consideration

WELLBASED counts with a total sample size of 1750 participants (*n* = 875 intervention group and *n* = 875 control group) distributed among the six study sites, with a minimum of 125 participants per arm per study site, as shown in Table 1. A 20% loss to follow-up (e.g. due to mortality, rehousing or impossibility to participate, as reflected in for this type of long-term studies) is expected [40]. This means the sample consists of *n* = 700 in the intervention group and *n* = 700 in the control group (total *n* = 1400) at 18-month follow-up. Equal standard deviations in the intervention and the control group are assumed, with alpha of 0.05 and power of 0.80. Thus, given six study sites with each an intervention group and control group, applying a correction factor to account for the clustered design, assuming an average cluster size of 117 citizens (1400/12) and an intra-class correlation coefficient of 0.02. For this expected overall sample size and assumptions, with regards to the continuous outcome measures (in particular, HRQoL) a difference of 0.28 standard deviation (SD) between the intervention and the control group can be detected at follow-up. This means that both at the European level, and in addition in each study site separately, small differences regarding the outcomes in the intervention group compared to the control group can be shown.

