### Data management and analysis

Data from all study sites are pseudo anonymized and combined in an online data platform (handled by INCLIVA). Erasmus University Medical Center is responsible for analysis and reporting. As the project will collect health-related data, special attention is attributed to the role of each partner in terms of controllers and processors, and to the organizational and technical measures to be put in place to ensure General Data Protection Regulation (GDPR) compliance. In addition, the risks associated to data processing will be defined in the Data Protection Impact Assessment (art. 35 GDPR) to be evaluated together with the Controllers’ Data Protection Officers. The data management plan includes procedures for ensuring a high-quality data standard, according to the FAIR principles: Findability, Accessibility, Interoperability, and Reusability [41]. All data are handled confidentially and scientific data are stored anonymously.

Descriptive statistics are used to describe participant characteristics in each study site and in the total study population, and to describe implementation outcomes in the study sites. Differences between T0, T1, T2 and T3 measurements are evaluated using multilevel linear regression analyses for continuous outcome variables and multilevel logistic regression analyses for dichotomous outcome variables. Interaction tests are performed for age, gender, living situation and education level to evaluate effects in subgroups. Statistical analyses are repeated for each study site separately. We consider a *P*-value of 0.05 or lower to be statistically significant. Analyses are performed according to the ‘intention to treat’ principle. An additional per protocol analyses is performed to evaluate the impact of the dose of the intervention received on outcomes.

A preliminary cost-effectiveness analysis is performed with the baseline measurement as control condition from a healthcare perspective. The healthcare costs per individual participant are calculated by multiplying resource use (e.g., doctor appointments, hospital admissions) with corresponding unit prices if available. Utility values are calculated using the EuroQol 5-level EQ-5D (EQ-5D-5L) to estimate the quality-adjusted life years (QALYs) [27]. EQ-5D-5L has demonstrated good measurement properties such as ceiling effects, reliability, and sensitivity [42].

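### The pooled 0.28 SD at 80% power ignores that the plan's own model has only 12 clusters: with 10 degrees of freedom, power is about 74% and the detectable difference about 0.30 SD

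*Protocol article*

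**What the plan says.** The Power consideration section supplies every input to a single pooled calculation:

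- Size: "WELLBASED counts with a total sample size of 1750 participants", 875 per arm. "A 20% loss to follow-up" is expected, which leaves 700 per arm ("total *n* = 1400) at 18-month follow-up").
- Variance: "Equal standard deviations in the intervention and the control group are assumed".
- Error rates: "with alpha of 0.05 and power of 0.80".
- Clustering: a correction factor is applied, "assuming an average cluster size of 117 citizens (1400/12) and an intra-class correlation coefficient of 0.02". The divisor 12 is six sites times two arms.
- Result: "a difference of 0.28 standard deviation (SD) between the intervention and the control group can be detected at follow-up".

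The section does not give the formula, whether the test is one- or two-sided, or the degrees of freedom. The Data management and analysis section plans multilevel regression and adds "We consider a *P*-value of 0.05 or lower to be statistically significant". It specifies neither the test statistic nor the levels of the model. The section on study population and eligibility lets sites randomise at either individual or cluster level.

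**The concern.** The calculation uses the 12 site-arm groups to inflate the variance, but its result fits only if that inflated variance is treated as known. If the site-arm group is the unit of clustering, the between-group variance has to be estimated from 12 units, six per arm. The reference distribution is then a t with 10 degrees of freedom. Its two-sided 5% critical value is 2.228, not 1.960, and the noise in the variance estimate costs further power.

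This is the only quantitative power statement for the main outcome, health-related quality of life. If it is optimistic, a null pooled result would be read as ruling out a smaller effect than the design can reliably detect. It is a printed numerical result, so it can be checked without a statistical analysis plan.

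**Working it through.** **Inputs** (all from Power consideration, except that a two-sided test is assumed): 700 analysed per arm; 12 clusters, mean size m = 117; ICC = 0.02; alpha 0.05; power 0.80; outcome in SD units.

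**1. Reproduce the plan's figure.**
- Design effect = 1 + (m − 1) × ICC = 1 + 116 × 0.02 = 3.32
- Effective n per arm = 700 / 3.32 = 210.8
- SE of the difference = √(2 × 3.32 / 700) = 0.0974 SD
- Detectable difference, normal quantiles = (1.960 + 0.842) × 0.0974 = 0.273 SD
- Power at 0.28 SD = Φ(0.28 / 0.0974 − 1.960) = Φ(0.915) = 82.0%

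So 0.28 is close to the large-sample result, with a small cushion. Variants tried at 80% power:

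| Variant | Detectable difference (SD) |
|---|---|
| t quantiles, individual-level df (1398) | 0.273 |
| Unequal site sizes from Table 1 | 0.274–0.275 |
| One-sided test | 0.242 |
| m = 145.8 (1750/12) with 700 analysed per arm | 0.296 |
| No clustering | 0.150 |

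The large-sample versions come closest to 0.28. The cluster-df versions below do not give it.

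**2. Same SE, with degrees of freedom from 12 clusters in two arms (12 − 2 = 10).**
- Non-centrality at 0.28 SD = 0.28 / 0.0974 = 2.875
- Power = P(t₁₀ with non-centrality 2.875 > 2.228) = 73.6%. A simulation of cluster means (200,000 runs) gives 73.7%.
- 80% power needs a non-centrality of 3.110, so 3.110 × 0.0974 = 0.303 SD
- With the unequal site sizes of Table 1, power at 0.28 SD is 72.9–73.4%

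**3. Within-site comparison (six pairs, 5 df).** Let ρ be the share of the between-cluster variance that is common to both arms of a site. It cancels in the within-site contrast, so SE = √{2 × [0.02(1 − ρ) + 0.98/117] / 6}. The article does not give ρ.

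| ρ | Power at 0.28 SD, 5 df |
|---|---|
| 0% | 64% |
| 25% | 72% |
| 50% | 81% |
| 75% | 91% |
| 100% | 98.5% (simulated) |

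At ρ = 0 the difference detectable at 80% power is 0.342 SD. Power reaches 80% at ρ of about 47%.

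**4. If the analysis used a normal critical value on 10 df:** P(|t₁₀| > 1.960) = 7.8%, against a nominal 5%.

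**5. Baseline adjustment (assumption: variance falls by 1 − r² at both levels).** Power at 0.28 SD with 10 df returns to 80% when 1 − r² = (0.28 / 0.303)² = 0.854, so r is about 0.38. At r = 0.5 it is 85%. The article gives no r.

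**The case against.** The strongest reply is that 12 independent clusters may not be the design. Sites may randomise individually, and Table 1 lists several districts or neighbourhoods for some of them (three in Valencia, two in Heerlen, five in Edirne). With individual allocation, or several clusters per site, 10 degrees of freedom would not apply and the design effect of 3.32 could be conservative. This stands as a limit on the finding. It does not rescue the printed figure, which was computed under the 12-cluster model.

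Second, the calculation is for one unadjusted follow-up comparison, whereas the main outcome is a change and the analysis uses repeated measurements. A baseline correlation of about 0.38 would restore 80%. That is plausible, but it is an assumption the power section does not invoke.

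Third, the shortfall is small beside the uncertainty in the ICC: with 10 df, power at 0.28 SD is 81% at an ICC of 0.015 and 61% at 0.03. That is true, but it does not justify leaving a known discrepancy in the figure.

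Two stronger readings are tempting and not supported. A reader might infer that true power is 64%, with 0.34 SD detectable, because each site has both arms. The power section states no pairing, and those figures charge for the pairing (5 df) while giving it no credit for shared site variance, so they are only the worst case. A reader might also infer that the planned test is anti-conservative. The article fixes no critical value or degrees-of-freedom method, a choice commonly left to a statistical analysis plan, so the error rate of about 8% is conditional and not a fault found in the text.

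**Conclusion.** The point holds for the pooled power figure. Under the article's stated assumptions (12 site-arm clusters of 117, ICC 0.02, 700 per arm, two-sided 5%, no covariate adjustment), power at 0.28 SD is about 74% rather than 80%, and the difference detectable at 80% power is about 0.30 SD. The chance of missing a true 0.28 SD effect is about 26% rather than 20%.

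That a large-sample formula was used is inferred from the match to 0.273 SD. The conclusion does not depend on it, because no choice of formula gives 0.28 SD 80% power once the 12 clusters set the degrees of freedom. For a within-site comparison, only the range of about 64% to about 98% can be supported. The correction is modest in size, but worth making because it concerns the main outcome and is cheap.

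**What to change.** - Restate the pooled detectable difference as about 0.30 SD at 80% power, or keep 0.28 SD and state power of about 74%. Name the formula, the sidedness and the degrees of freedom.
- In the pooled multilevel model, specify Kenward-Roger or Satterthwaite degrees of freedom at site-arm level wherever the site-arm group is the clustering unit.
- If arms are to be compared within site, state the assumed share of between-cluster variance common to both arms and give power for that value. Show 0.34 SD only as the worst case, with no sharing.
- If baseline adjustment is relied on to recover power, state the assumed correlation.
- Where sites randomise individually or in several clusters each, redo the calculation for that design.

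Cost: wording, one software option, and a slightly less favourable stated figure. No added participants or data.

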VALENCIA (SPAIN)	Three districts with high sociodemographic vulnerability, due to an aged population, lower incomes than the city average and higher percentages of people at risk of poverty	177 participants per study arm
HEERLEN (THE NETHERLANDS)	Social housing tenants from two districts in the northern part of the city with low incomes, high energy bills, low energy measures and bad housing conditions	156 participants per study arm
EDIRNE (TURKEY)	Low-income households in five neighbourhoods, where vulnerable groups, including Roma, are highly represented	125 participants per study arm
JELGAVA (LATVIA)	The most vulnerable households, described by low income levels, long-term unemployment (> 1 year), disabled people, poor housing quality, single-parent families, pensioners (especially suffering loneliness), and provided by the municipality	146 participants per study arm
LEEDS (United Kingdom)	Social housing tenants, managed by the City Council, with poor housing quality, classified as energy efficiency band D or below. Target group has different vulnerabilities: low income, older people, disabled people, single parents and recent migrants	125 participants per study arm
OBUDA (HUNGARY)	Vulnerable inhabitants of Óbuda-Békásmegyer, the 3^rd^ district of Budapest, characterised by low incomes, victims of domestic violence and/or drug abuse, households with disabled and/or chronically ill members, unemployed members, and single mothers	146 participants per study arm

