### Study population and eligibility to participate in the study

All participants who provide informed consent are enrolled in the study. We aim to include 1750 participants in total. Each study site allocates at least 125 participants to the intervention condition and 125 participants to the control condition. Detailed numbers of participants per study site are presented in Table 1. Study sites might apply randomization at individual or cluster level to create intervention and control condition.

Study participants are included if they: (i) are aged ≥ 18 years old, (ii) are in a vulnerable situation (e.g. unemployed, low income, single parents, parents with dependent children, seniors (65 +) with dependency conditions, seniors (65 +) living alone, people with disabilities attended by social services, belonging to a minority, migrant situation), (iii) living in energy poverty conditions, and (vi) belonging to the recruitment sites identified by the local partners for the study. The research assistant recruits potential participants in collaboration with local agencies that work in the catchment area. Together they determine energy poverty conditions (criterion iii), based on their knowledge of and experience with the target population. The primary indicators suggested by EU Energy Poverty Observatory (EPOV) are used as guideline to assess the energy poverty status. EPOV established the following criteria:i.arrears on utility bills;ii.low absolute energy expenditure (below half of the national median (M/2));iii.high share of energy expenditure in income (double of the national median share of energy expenditure in income (2 M)) andiv.inability to keep home adequately warm [26].

Persons are not eligible to participate if they have previously been beneficiaries of a previous similar intervention, cannot adequately participate in the intervention actions proposed in the study site (e.g. intellectual disabilities, severe language limitations) or are illegally connected to the electricity grid.

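### The 0.28 SD detectable difference comes from the pooled sample and does not carry over to each study site, where the plan's own inputs give about 0.33 to 0.40 SD

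*Protocol article*

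**What the plan says.** The Power consideration section starts from 875 participants per arm over six sites, "with a minimum of 125 participants per arm per study site". It expects 20% loss, which leaves 700 per arm at 18 months. With alpha 0.05, power 0.80, equal SDs, an average cluster of 117 (1400/12) and an ICC of 0.02, it gives a detectable difference of 0.28 SD, explicitly for the overall sample.

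The next sentence presents a consequence of that figure. It covers the European level and then adds that "in addition in each study site separately, small differences regarding the outcomes in the intervention group compared to the control group can be shown". No site-level calculation is shown.

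The eligibility section sets the floor per site: "Each study site allocates at least 125 participants to the intervention condition and 125 participants to the control condition". Table 1 gives the planned numbers per arm: Valencia 177, Heerlen 156, Jelgava and Obuda 146 each, Edirne and Leeds 125 each.

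The site-level claim supports a planned analysis. Under Data management and analysis: "Statistical analyses are repeated for each study site separately". The general significance threshold of 0.05 follows directly, and the site analyses are not labelled exploratory.

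**The concern.** A detectable difference depends on the number of people compared. A figure obtained from 700 per arm cannot be passed on to a comparison of 100 to 142 per arm without a new calculation. The pooled design effect might seem to leave room for it, since it reduces 700 to an effective size of about 211 per arm. Every site is still well below 211, even if it is charged no clustering penalty at all.

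What is at stake is how the six site results are read. The Strengths section looks forward to comparing interventions and outcomes across countries. A reader who has been told that every site can show small differences may take a non-significant site result as evidence that the programme had no effect there. In fact the chance of missing a true difference of 0.28 SD in a site is between about one in three and one in two.

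**Working it through.** **Inputs.** Site sizes from Table 1. Loss of 20%, alpha 0.05, power 0.80, ICC 0.02 and cluster size 117 from Power consideration. Sidedness is not stated, so two-sided is assumed. Effects are in SD units.

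**Step 1: reproduce the plan's figure.** The design effect is 1 + (117 − 1) × 0.02 = 3.32, so the effective size is 700 / 3.32 = 210.8 per arm. The detectable difference is (1.960 + 0.842) × √(2 / 210.8) = 0.273 SD. Power at 0.28 SD is Φ(0.28 / √(2 / 210.8) − 1.960) = 82%. The stated 0.28 SD is confirmed and slightly conservative.

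**Step 2: apply the same formula to one site.** Here n is 0.8 times the Table 1 number per arm, with no design effect and no baseline adjustment:

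- detectable difference = 2.802 × √(2/n)
- power at 0.28 SD = Φ(0.28 / √(2/n) − 1.960)

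| Site | Recruited per arm | Completers per arm | Detectable difference (SD) | Power at 0.28 SD |
|---|---|---|---|---|
| Edirne, Leeds | 125 | 100 | 0.396 | 51% |
| Jelgava, Obuda | 146 | 116.8 | 0.367 | 57% |
| Heerlen | 156 | 124.8 | 0.355 | 60% |
| Valencia | 177 | 141.6 | 0.333 | 65% |

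**Step 3: size needed.** For 0.28 SD at 80% power, n = 2 × (2.802 / 0.28)² ≈ 200.3, so 201 completers per arm. That is 201 / 0.8 = 251.25, or 252 recruited per arm. The largest site plans 177.

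**Step 4: sensitivity to the assumptions.**

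- One-sided alpha 0.05: (1.645 + 0.842) × √(2/n) gives 0.352 SD at 100 per arm and 0.296 SD at 141.6.
- No loss to follow-up: 2.802 × √(2/125) = 0.354 SD and 2.802 × √(2/177) = 0.298 SD. No site reaches 0.28 SD under either change alone.
- Baseline adjustment multiplies the figure by √(1 − r²). The article gives no r. Assuming 0.5, 0.6 or 0.7, a site with 100 per arm detects 0.34, 0.32 or 0.28 SD, and Valencia 0.29, 0.27 or 0.24 SD. Reaching 0.28 SD needs r of about 0.71 at 100 per arm and about 0.54 in Valencia.

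**Step 5: a conditional case.** Suppose a site gave one whole area to each arm and the ICC of 0.02 applied to those areas. The design effect would be 1 + 99 × 0.02 = 2.98 at 100 per arm and 1 + 140.6 × 0.02 = 3.81 at 141.6. The nominal detectable difference would be 0.396 × √2.98 = 0.68 SD and 0.333 × √3.81 = 0.65 SD. With one area per arm, the arm effect could also not be separated from the area effect.

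**The case against.** The best defence has three parts.

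First, the article never defines a small difference, so 0.33 to 0.40 SD might qualify. This does not rescue the sentence. The site claim is presented as following from 0.28 SD, which is the only benchmark given.

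Second, the main outcome is change in quality of life and the analysis is a multilevel model over four time points, so an unadjusted comparison at 18 months understates the precision available. This part stands. At r = 0.7 the four larger sites would fall below 0.28 SD and the two smallest would sit at 0.283. But the power section invokes no such gain and gives no correlation, so the claim as printed does not rest on it.

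Third, the site analyses only repeat the pooled one, and the 0.05 threshold is a general convention, not a decision rule for each city. That is fair, and it limits the consequence. It does not make the power statement correct.

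Two stronger readings should be resisted. A reader might infer that every site detects 0.40 SD at best. That figure belongs to Edirne and Leeds only, and with baseline adjustment it is not a best case even there. A reader might also infer that site comparisons are hopelessly confounded with area, pointing to Heerlen's recruitment of "Social housing tenants from two districts in the northern part of the city". Table 1 names those districts as the source of the target group and does not say that each forms one arm. The eligibility section leaves randomization at individual or cluster level open and gives no number of clusters per site. The 12-group correction is written for the pooled sample. The 0.65 to 0.68 SD figures therefore hold only under the condition in step 5.

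**Conclusion.** The point holds as a wrong statement about site-level power. On the plan's own sizes, loss, alpha and power, no site reaches 80% power at 0.28 SD. Detectable differences run from 0.33 to 0.40 SD and power at 0.28 SD from 51% to 65%. These figures assume a two-sided test, no baseline adjustment and no clustering within site. A baseline correlation of about 0.71 would be needed before all six sites reached 0.28 SD, and the article does not claim one.

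The pooled calculation is sound. The fault is the unsupported step from the pooled sample to the single site. The documents do not establish that any site allocates one area per arm, so inseparability of arm and area remains a conditional warning.

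**What to change.** In Power consideration, limit the claim to the pooled sample and replace the site-level clause with a statement of this kind: within a single site, with 100 to 142 completers per arm and individual allocation, differences of about 0.33 to 0.40 SD are detectable with 80% power, before any baseline adjustment. If the authors wish to rely on baseline adjustment, they should state the assumed correlation and the resulting figure per site. If any site allocates whole areas, that site should be named and the individual-allocation figure not applied to it.

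In Data management and analysis, label the repeated site analyses exploratory and report them as estimates with confidence intervals. Judge any difference between sites by a site-by-arm term in the pooled model, not by which sites pass 0.05.

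The cost is some rewording, one added model term and a less favourable stated figure. Recruitment and data collection do not change.
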